### Randomization

A two-staged block randomization will be used with allocation concealment from the active research team via the use of sealed opaque envelopes. The first randomization will be in blocks of six, with separate sex randomization. Second randomization will be in blocks of four, again with separate sex randomization. Eligible participants will be notified via email and invited to complete an online demographic and lifestyle behaviors questionnaire, as detailed in Table 1, prior to stage 1 randomization to either online control (n=200) or face-to-face (n=400) groups. Stage two randomization will occur at the second study visit to assign face-to-face participants to either tailored feedback or active control. Due to the nature of the intervention, it is not possible to blind participants or researchers to the intervention group postallocation. Sequence generation will be conducted by a biostatistician not involved in the implementation of the trial on site using a randomization table created in Stata (version 15, StataCorp, College Station, TX). The electronic file will be kept in a secure password-protected server by the statistician.

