### Data-Collection Procedures

Following stage 1 randomization, tailored feedback and active control participants will be invited to attend two data-collection sessions with the research team, approximately 1 week apart. At the first baseline visit, participants will receive training in the use of the 4-day mFR [26-28] and hip-worn GT3X+ accelerometer (Actigraph, Pensacola, FL). During the second study visit, participants will return their accelerometer and be interviewed to clarify the content of their mFR images. At this visit, height, body mass, waist, and hip girth will be measured according to the standard protocol [29], and an aerobic fitness test (6-minute walk test) will be conducted [30]. The same assessments will be repeated at 6 and 12 months, along with additional online assessments for all groups (Table 1) at the same time points. All participants will have access to the LiveLighter website resources throughout the intervention and will be encouraged to use the materials that include evidence-based healthy recipes and meal plans [25].

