### Dietary Assessment

For the face-to-face (active control and tailored feedback) groups, diet will be recorded using the mFR app with inclusion of a fiducial marker (an object of known shape, size, and color) [26] in the image to aid in portion size estimation. “Before eating” and “after eating” images of all foods and beverages consumed over four consecutive days, including one weekend day, will be captured at baseline, 6 months, and 12 months for each participant. In addition, at 6, 12, 18, and 24 weeks, the tailored feedback group will complete a 1-day mFR to encourage self-monitoring of food intake to facilitate feedback. All images will be automatically uploaded to a secure cloud server residing on the Curtin University Bentley campus via Wi-Fi or 3G/4G network. All images will be assessed by a research dietitian for serves of fruits, vegetables, and energy-dense nutrient-poor (EDNP) foods and beverages according to the Australian Guide to Healthy Eating standard serves (one serve=600 kJ) [45].

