6 months	4-d summary from 6-mo mFR showing daily serves with comparison against baseline diet mFR food images showing participants the source of their EDNP foods, sugary drinks, alcohol, fruits, and vegetables Tailored feedback against recommended serves + goals targeting: Avoid or limit EDNP foods, sugary drinks, and alcohol Eat less at meals or snacks (except for fruit and vegetables) Eat less often (eg, limit snacking) Tailored support for unhelpful behaviors: Emotional/restrained/uncontrolled eating (identified in the three-factor eating questionnaire) Tailored feedback on how to make a healthy diet habitual based on habit index score	Face-to-face visit summary: comparison with baseline (body mass and aerobic fitness) 7-d visual summary (average) for step count, MVPA, and hourly movement + comparison with baseline for each movement goal Future goal setting for translation phase Tailored guidance on how to make PA habitual based on habit index score	Review behavior goals Self-comparison Feedback on behavior Tailored personalized message Prompt self-monitoring of behavior Goal setting Discrepancy between current behavior and recommendations
12 months	4-d summary from 12-mo mFR showing daily serves with comparison against baseline Tailored feedback against recommended serves + target goals	Face-to-face visit tabulated summary: comparison with baseline and 6 mo (body mass and aerobic fitness) 7-d visual summary (average) for step count, MVPA, and hourly movement + comparison with baseline and 6 mo for each movement goal Future goal setting for translation phase	Review behavior goals Self-comparison Social comparison with study participants Feedback on behavior Tailored personalized message Prompt self-monitoring of behavior Goal setting Discrepancy between current behavior and recommendations

^a^mFR: mobile food record.

^b^EDNP: energy-dense nutrient poor.

^c^ADG^:^ Australian Dietary Guidelines.

^d^MVPA: moderate-to-vigorous physical activity.

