### Tailored Dietary Feedback

Tailored dietary feedback will be formulated by the research dietitian based on food group analysis of the 4-day mFR. Feedback will focus on key messages encouraging daily energy reduction of 2000 kJ by avoiding or limiting EDNP foods, sugar-sweetened beverages, and alcohol; eating less at meals or additional snacks (except for salad and vegetables); and eating less often. Food group serves will be categorized for each participant based on three defined target zones (not achieved, almost achieved, and achieved). A template will be used for each dietary feedback email, modified according to the results of each participants’ dietary analysis. For EDNP serves, the template will be modified according to dietary intake to indicate average daily serves of “junk” foods, sugary drinks, and alcohol and kilojoule intake. Participants will be shown an image of their dietary sources of EDNP food and beverages. For fruit and vegetable serves, a scripted message will be devised for three levels of intake: (1) low: 0 to <3.5 serves of fruits and vegetables, (2) medium: 3.5 to <7 serves of fruits and vegetables, and (3) meeting the recommendation: at least 2 serves of fruits and 5 serves of vegetables per day. Individual mFR images will be incorporated into email templates to illustrate the sources of EDNP foods, fruits, and vegetable serves. Two to three suggested modifications will be provided to each participant to support them in achieving the daily energy-reduction goal.

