### Statistical Analysis

The following primary outcome variables will be measured at baseline and 12 months of the intervention: changes in body mass, EDNP food and beverage consumption (sugar-sweetened beverages, alcohol, and take away and other “junk” foods), and daily minutes spent in MVPA. Secondary outcome variables include changes in fruit and vegetable serves and daily minutes spent in sedentary activity. Outcomes will identify characteristics of responders who remained engaged and reported improvements in key behaviors and quantify resource use associated with each arm of the study, which will be used in an economic evaluation of tailored feedback. Data on change in outcome variables in each of the two groups will be compared using analysis of covariance. Assumptions of the analyses will be assessed by examining residuals. Data will be transformed if assumptions of the analyses are not satisfied. Possible covariates considered will include age, sex, country of birth, ethnicity, highest education level, socioeconomic index for area, and baseline value of the variable analyzed. *P*-values < .05 will be considered statistically significant. Effect size of differences between treatment and control will be expressed as adjusted mean difference and associated 95% CIs. Data on change in outcome variables postintervention and follow-up time points will be converted into binary categorical variables and analyzed using multivariable logistic regression and generalized estimating equations. Odds ratio and associated 95% CIs will be reported. The analyses will identify characteristics of participants who are least likely to change their consumption of EDNP foods, PA, and BMI, thereby identifying target groups for future health promotion interventions.

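### The protocol rules out blinding of researchers without exempting image coding, so the human-scored EDNP outcome that the sample size rests on is open to arm-aware scoring by the role that also writes the tailored feedback

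*Protocol article*

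**What the plan says.** All references are to the protocol article.

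- **Blinding.** Randomization gives the nature of the intervention as the reason why "it is not possible to blind participants or researchers to the intervention group postallocation". No exception is made for anyone who assesses outcomes.
- **Who scores diet.** Dietary Assessment: "All images will be assessed by a research dietitian for serves of fruits, vegetables, and energy-dense nutrient-poor (EDNP) foods and beverages". Portion size is estimated from before-and-after images with the aid of a fiducial marker.
- **Who writes the feedback.** Tailored Dietary Feedback: "Tailored dietary feedback will be formulated by the research dietitian based on food group analysis of the 4-day mFR".
- **The same records serve both purposes.** The 6-month email in Table 2 contains a "4-d summary from 6-mo mFR showing daily serves with comparison against baseline diet". The 12-month email likewise draws on the 12-month record.
- **Status of the outcome.** Statistical Analysis lists as primary "changes in body mass, EDNP food and beverage consumption (sugar-sweetened beverages, alcohol, and take away and other “junk” foods), and daily minutes spent in MVPA". Power bases the sample size on EDNP serves alone.
- **Records in one arm only.** Dietary Assessment: "at 6, 12, 18, and 24 weeks, the tailored feedback group will complete a 1-day mFR".
- **Timing of allocation.** Randomization: "Stage two randomization will occur at the second study visit to assign face-to-face participants to either tailored feedback or active control". Data-Collection Procedures has participants, at that same visit, "be interviewed to clarify the content of their mFR images", and repeats the assessments at 6 and 12 months.

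**The concern.** EDNP serves are a human reading of food images: what the food is, how large the portion is, and how many 600 kJ serves it makes. A coder who knows the arm can resolve doubtful cases differently in the two face-to-face groups. The role that does this reading also advises tailored feedback participants to cut exactly these foods, and draws that advice from the same 4-day records that supply the outcome.

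A systematic coding difference between arms adds directly to the estimated treatment difference. Adjustment for covariates cannot remove it, because it is aligned with arm. The comparison at stake is tailored feedback against active control, since the online control group has no mFR. Body mass is weighed and moderate-to-vigorous activity is device-recorded in these two groups, so the exposure is specific to the image-coded diet outcomes. Those are EDNP serves and, among the secondary outcomes, fruit and vegetable serves.

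**Working it through.** **Step 1: does the stated reason cover image coding?** The reason given is the nature of the intervention. Participants know whether they receive emails, and whoever writes an email knows who gets it. Coding is different: images go automatically to a secure server and are assessed from there. Nothing in the nature of the intervention requires the coder to see the arm while counting serves. The sentence is therefore broader than its reason.

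**Step 2: is baseline exposed?** Stage two allocation and the baseline clarification interview fall at the same visit, and their order is not stated. Images are already on the server by then, so they could be coded before or after allocation. Baseline is exposed only if coding is done or finalised after that visit. This matters because the outcome is a change and the baseline value is a possible covariate.

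**Step 3: the plan's own figures.** Inputs from Power: difference 0.6 serves/day, 90% power, 5% significance (taken as two-sided; sidedness is not stated), 200 per group, 20% drop-out.
- 0.6 × 600 kJ = 360 kJ, as stated.
- 160 / 0.8 = 200, so 200 recruited leaves 160 per group after drop-out.
- No SD is given, so the sample size cannot be reproduced. It can be solved backwards, treating the stated difference as a difference in means.

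SE = 0.6 / (1.960 + 1.282) = 0.185 serves/day.

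Implied SD = SE / √(2/n):
- n = 200 per group analysed: 0.185 / 0.100 = 1.85
- n = 160 per group analysed: 0.185 / 0.1118 = 1.66

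Both readings give the same SE, so the results below do not depend on which was meant.

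**Step 4: effect of a differential coding shift.** Suppose there is no true effect and arm-aware scoring shifts the tailored feedback minus active control difference by b. Then

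type I error = Φ(−1.96 + b/SE) + Φ(−1.96 − b/SE).

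| Assumed b (serves/day) | kJ/day | Share of 0.6 target | Type I error |
|---|---|---|---|
| 0 | 0 | 0% | 5.0% |
| 0.05 | 30 | 8% | 5.8% |
| 0.1 | 60 | 17% | 8.4% |
| 0.2 | 120 | 33% | 19% |
| 0.3 | 180 | 50% | 37% |

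For b = 0.2: b/SE = 1.08, so Φ(−0.88) + Φ(−3.04) = 0.190 + 0.001 = 0.191.

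The values of b are assumptions. The documents give no figure for coder bias.

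**The case against.** The strongest reply is that a journal article condenses the full protocol, and coding procedure is the kind of detail it leaves out. Coding also has some structure: a fiducial marker for portion size and a standard 600 kJ serve. Two of the three primary outcomes do not depend on a coder in these arms. The structure and the other outcomes limit the damage. The appeal to omitted detail does not succeed, because the article does not stay silent. It says affirmatively that researchers cannot be blinded.

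Several stronger readings are tempting, and the text does not support them:

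- **One person does both tasks.** The article names one role, not one individual, and does not say how many dietitians there are. That the coder sees the arm follows from the general blinding sentence; Dietary Assessment does not say so.
- **Tailored feedback records are coded first.** The first email is due within 2 weeks of baseline, but no coding order or schedule is given for either group.
- **Baseline coding necessarily follows allocation.** It may, but automatic upload makes earlier coding possible.
- **The bias must favour the intervention.** Coder expectation could push that way, but the documents hold no evidence on direction or size.
- **Masking costs no staff.** No staffing is given, so nothing can be claimed either way.

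It is also fair to object that masking would be incomplete. The clarification interview at 6 and 12 months remains an unmasked human step. A dietitian who has handled the 1-day records of the tailored feedback group, or placed participants' images in emails, may recognise some later images. That limits what the remedy can achieve, but it is no reason to leave coding unmasked.

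**Conclusion.** The point holds in this form: the protocol's blanket statement leaves the scorer of the EDNP outcome unmasked, the same role writes the intervention feedback from the same records, and the reason given does not justify extending the statement to image coding. EDNP is one of three primary outcomes and the only one on which the sample size is based.

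The size is illustrative. A differential shift of 0.1 to 0.2 serves/day, a sixth to a third of the target, would take the type I error from 5% to between about 8.4% and 19%. This rests on the assumed shift, a two-sided test, and the SE of 0.185 implied by the Power section. The point should be acted on. It does not call the sample size or the other two primary outcomes into question.

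**What to change.** 1. Replace the blinding sentence with: *participants and intervention staff are not blinded; mFR image coding is masked to arm*.
2. At baseline, 6 and 12 months, release the 4-day image sets of the tailored feedback and active control groups to the coder under neutral record numbers. Use mixed rolling batches, which fit the staggered recruitment.
3. Lock the food-group serves before unmasking tailored feedback records to write the emails.
4. Use the 1-day records of the tailored feedback group for feedback only, never as outcome data.
5. Where more than one dietitian is already available, the coder of a participant's outcome records should not handle that participant's feedback.
6. State that masking is partial, naming the clarification interview and possible recognition of images.

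The cost is a workflow step on the existing server, coding of active control records alongside tailored feedback records, and a tighter turnaround for the email due within 2 weeks of baseline. Sample size, visits and intervention content do not change.

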### Data-Collection Procedures

Following stage 1 randomization, tailored feedback and active control participants will be invited to attend two data-collection sessions with the research team, approximately 1 week apart. At the first baseline visit, participants will receive training in the use of the 4-day mFR [26-28] and hip-worn GT3X+ accelerometer (Actigraph, Pensacola, FL). During the second study visit, participants will return their accelerometer and be interviewed to clarify the content of their mFR images. At this visit, height, body mass, waist, and hip girth will be measured according to the standard protocol [29], and an aerobic fitness test (6-minute walk test) will be conducted [30]. The same assessments will be repeated at 6 and 12 months, along with additional online assessments for all groups (Table 1) at the same time points. All participants will have access to the LiveLighter website resources throughout the intervention and will be encouraged to use the materials that include evidence-based healthy recipes and meal plans [25].

### Research Study Database

A purpose-built research study database will be developed based on findings from prior research [44] using a Microsoft Access database platform to track the progress of the study participants at time points outlined in Tables 1 and 2. The database will have the functionality of sending autogenerated emails containing study information and links. To track progress of the tailored feedback group requiring face-to-face visits, information regarding upcoming appointment date and time and relevant survey URLs will be sent using autogenerated emails. To remind participants of upcoming appointments, email and mobile SMS prompts will be sent from the study database using “Email to SMS” technology.

An online survey tool (Qualtrics) will be used to capture demographic information as outlined in Table 1. The study database will have the functionality of importing data to automatically update participant status with respect to their study compliance. The system will prompt reminders via email and SMS for participants who have not yet completed their tasks.

### Dietary Assessment

For the face-to-face (active control and tailored feedback) groups, diet will be recorded using the mFR app with inclusion of a fiducial marker (an object of known shape, size, and color) [26] in the image to aid in portion size estimation. “Before eating” and “after eating” images of all foods and beverages consumed over four consecutive days, including one weekend day, will be captured at baseline, 6 months, and 12 months for each participant. In addition, at 6, 12, 18, and 24 weeks, the tailored feedback group will complete a 1-day mFR to encourage self-monitoring of food intake to facilitate feedback. All images will be automatically uploaded to a secure cloud server residing on the Curtin University Bentley campus via Wi-Fi or 3G/4G network. All images will be assessed by a research dietitian for serves of fruits, vegetables, and energy-dense nutrient-poor (EDNP) foods and beverages according to the Australian Guide to Healthy Eating standard serves (one serve=600 kJ) [45].

### Physical Activity Assessment

Physical activity and sedentary behavior will be assessed with a hip-worn Actigraph GT3X+ accelerometer to quantify change in average MVPA and sedentary time for the face-to-face (active control and tailored feedback) groups. The accelerometer will also enable the assessment of sleep. The participants will be instructed to wear the accelerometer on their right hip 24/7 for 7 consecutive days. Commonly used cut-off points will be used to classify each minute of accelerometer data as sedentary (<100 counts per minute) [46], light intensity (100-1951 counts per minute), moderate intensity (1952-5724 counts per minute), or vigorous intensity (>5724 counts per minute) [47].

A wrist-worn activity monitor (Fitbit Charge 2) will be provided to the tailored feedback group to enable 24/7 continuous self- and researcher monitoring of step count, MVPA, and hourly movement to inform PA feedback. Participants will be asked to wear the monitor at night to enable the assessment of sleep. With informed consent, activity monitor data will be automatically imported into a back-end research platform (Fitabase) to facilitate PA behavior data monitoring, extraction, and analysis by researchers.

### Intervention Content

Intervention content for diet and PA will be informed by evidence-based guidelines [48-50] to support weight loss through reduced energy intake and increased PA. The behavioral intervention technology framework Capability, Opportunity, Motivation, and Behaviour (COM-B) model; self-determination theory; and previous research will guide the development of intervention behavior-change strategies [20,22,51,52]. These include self-monitoring, goal setting, motivation enhancement (including positive reinforcement in tailoring communications and incentives), and feedback to increase likelihood of engagement [52]. To refine the intervention features and content, formative focus group studies with 56 consumers and health professionals were conducted prior to the intervention.

**Table 1 table1:** Frequency of assessment of variables in the ToDAy study for the tailored feedback, active control, and online control groups.

Variables	Group	Baseline	6 months	12 months
Health status EQ-5D^a^, a 5-item scale to assess utility and health-related quality of life [31]	TF^b^, AC^c^, OC^d^	Yes	Yes	Yes
Height and body mass (self-report)	TF, AC, OC	Yes	Yes	Yes
Height, body mass, body mass index, waist, and hip girth^e^	TF, AC	Yes	Yes	Yes
Sociodemographics and personal characteristics assessed via questions on sex, age, eating behavior, educational level, country of birth, ethnicity, socioeconomic status, and financial status	TF, AC, OC	Yes	Yes	Yes
Australian eating survey, an online food frequency questionnaire with options for automated dietary feedback previously validated in adults [32]	TF, AC, OC	Yes	Yes	Yes
Dietary intake assessed by 4-day mFR^f^	TF, AC	Yes	Yes	Yes
Mobile food record usability to assess user feedback and method preference [33,34]	TF, AC	Yes	Yes	Yes
Three-factor eating survey to measure factors associated with eating behavior: cognitive restraint of eating, disinhibition, and hunger [35]	TF, AC	Yes	—^g^	—
Self-reported physical activity assessed via The International Physical Activity Questionnaire (short form) [36]	TF, AC, OC	Yes	Yes	Yes
Cardiorespiratory fitness determined by distance covered in the 6-minute walk test to assess change in submaximal exercise capacity [30]	TF, AC	Yes	Yes	Yes
Physical activity and sedentary behavior assessed with GT3X+ Actigraph accelerometer to quantify change in average minutes of moderate-to-vigorous physical activity and sedentary time	TF, AC	Yes	Yes	Yes
Sleep-quality assessment using the Pittsburgh Sleep Quality Index seven-component evaluation of sleep quality, latency, duration, habitual sleep efficiency, sleep disturbances, use of sleeping medications, and daytime dysfunction over the previous month [37]	TF, AC	—	Yes	Yes
Depression, anxiety, stress scale, with 21 self-report items to assess severity of depression, anxiety, and stress [38]	TF, AC, OC	Yes	Yes	Yes
Fear of negative evaluation, with twelve 5-point items to assess concern about being perceived unfavorably [39]	TF, AC	Yes	—	—
Social desirability to measure social approval and acceptance [40]	TF, AC	Yes	—	—
Habit Index Score [41]	TF, AC	Yes	Yes	Yes
Weight-loss history, an 8-item tool to assess previous weight-loss history [42]	TF, AC, OC	—	—	—
Technology use questionnaire to assess duration and frequency of technology use indicative of sedentary behaviors [43]	TF, AC, OC	Yes	Yes	Yes
Feedback evaluation questionnaire for activity-monitor usability, physical activity, and dietary feedback evaluation	TF	—	Yes	Yes

^a^EQ-5D: EuroQol-5D.

^b^TF: tailored feedback.

^c^AC: active control.

^d^OC: online control.

^e^Height measured in centimeters via stadiometer using stretch stature method, body mass measured in kilograms via weighing scale in minimal clothing at similar time of the day, body mass index calculated as kilogram per meter squared, waist measured in in centimeters via tape at the narrowest point between the lower costal border and iliac crest, and hip girth measured via tape at the level of the greatest posterior protuberance.

^f^mFR: mobile food record.

^g^Not assessed.

**Table 2 table2:** Overview of frequency, content, and technique of tailored email feedback for diet and physical activity behaviors.

Feedback frequency	Feedback content		Behavior-change techniques [52]
	Diet	Physical activity	
2 weeks	4-d summary (average + range) from mFR^a^ showing average daily serves (kilojoule equivalent) for EDNP^b^ foods, sugary drinks, and alcohol Example ADG^c^ serves for EDNP foods, sugary drinks, and alcohol mFR food images showing participants the source of their EDNP foods, sugary drinks, and alcohol serves Tailored feedback + goals based on key messages: avoid EDNP foods, avoid sugary drinks, avoid alcohol	Introduction of movement goals and wearable activity monitor guide 7-d summary (average + range) for step count, MVPA^d^, and hourly movement Tailored feedback + guidance based on movement goal achievement (not met, almost met, and met)	Instruction on how to perform the behavior Feedback on behavior Tailored personalized message Prompt self-monitoring of behavior Goal setting Discrepancy between current behavior and recommendations
4 weeks	Weight loss goal of 10% 4-d summary (average + range) from mFR showing average daily serves for fruit and vegetables Example ADG serves for fruit and vegetables mFR food images showing participants the source of their fruit and vegetable intake Tailored feedback against recommended serves + goals to increase fruit and vegetable serves	7-d visual summary of challenge movement goal, with comparison to goal target Activity tips to assist with weight loss linked to movement goals	Review behavior goal Feedback on behavior Action planning Prompt self-monitoring of behavior Discrepancy between current behavior and recommendations
6 weeks	1-d summary from 6-wk mFR showing daily serves of EDNP foods, sugary drinks, alcohol, and fruits and vegetables Comparison against baseline diet mFR food images showing participants the source of their EDNP foods, sugary drinks, alcohol, fruits, and vegetables Tailored feedback against recommended serves + goals targeting: Avoid or limit EDNP foods, sugary drinks and alcohol Eat less at meals or snacks (except for fruit and vegetables) Eat less often (eg, limit snacking)	Review of the movement goals 7-d summary (average + range) for step count, MVPA, and hourly movement Comparison with baseline activity for each movement goal Tailored feedback + guidance based on movement goal achievement (not met, almost met, and met)	Review behavior goals Self-comparison Feedback on behavior Tailored personalized message Prompt self-monitoring of behavior Goal setting Discrepancy between current behavior and recommendations
12 weeks	1-d summary from 12-wk mFR showing daily serves of EDNP foods, sugary drinks, alcohol mFR food images showing participants the examples of meal or snack behaviors Tailored feedback + goals targeting: Eat less at meals or snacks (except for fruits and vegetables) Avoid or limit snacking	Reiteration of energy deficit goal + instruction on how to create an energy deficit via energy output 7-d summary (average + range) of MVPA goal Tailored feedback + guidance based on movement goal achievement (not met, almost met, and met) Translation of MVPA into energy output	Review of outcome goal Review behavior goal Feedback on behavior Tailored personalized message Prompt self-monitoring of behavior Goal setting Discrepancy between current behavior and recommendations
18 weeks	Reiteration of dietary goals + instruction on how to create an energy deficit from diet (eg, reduction in EDNP food serves) Reiteration of “what’s a serve of EDNP foods” Reminder of dietary goals + suggestions on how to achieve them: Avoid or limit EDNP foods, sugary drinks, and alcohol Eat less at meals or snacks (except for fruit and vegetables) Eat less often (eg, limit snacking)	Reiteration of energy-deficit goal + instruction on how to create an energy deficit via energy output 7-d summary (average + range) of MVPA goal Tailored feedback + guidance based on movement goal achievement (not met, almost met, and met) Translation of MVPA into energy output Reminder of movement goal targets linked to creating an energy deficit	Review of outcome goal Review behavior goals Feedback on behavior Tailored personalized message Goal setting Discrepancy between current behavior and recommendations
6 months	4-d summary from 6-mo mFR showing daily serves with comparison against baseline diet mFR food images showing participants the source of their EDNP foods, sugary drinks, alcohol, fruits, and vegetables Tailored feedback against recommended serves + goals targeting: Avoid or limit EDNP foods, sugary drinks, and alcohol Eat less at meals or snacks (except for fruit and vegetables) Eat less often (eg, limit snacking) Tailored support for unhelpful behaviors: Emotional/restrained/uncontrolled eating (identified in the three-factor eating questionnaire) Tailored feedback on how to make a healthy diet habitual based on habit index score	Face-to-face visit summary: comparison with baseline (body mass and aerobic fitness) 7-d visual summary (average) for step count, MVPA, and hourly movement + comparison with baseline for each movement goal Future goal setting for translation phase Tailored guidance on how to make PA habitual based on habit index score	Review behavior goals Self-comparison Feedback on behavior Tailored personalized message Prompt self-monitoring of behavior Goal setting Discrepancy between current behavior and recommendations
12 months	4-d summary from 12-mo mFR showing daily serves with comparison against baseline Tailored feedback against recommended serves + target goals	Face-to-face visit tabulated summary: comparison with baseline and 6 mo (body mass and aerobic fitness) 7-d visual summary (average) for step count, MVPA, and hourly movement + comparison with baseline and 6 mo for each movement goal Future goal setting for translation phase	Review behavior goals Self-comparison Social comparison with study participants Feedback on behavior Tailored personalized message Prompt self-monitoring of behavior Goal setting Discrepancy between current behavior and recommendations

^a^mFR: mobile food record.

^b^EDNP: energy-dense nutrient poor.

^c^ADG^:^ Australian Dietary Guidelines.

^d^MVPA: moderate-to-vigorous physical activity.

At randomization, tailored feedback participants will be informed of feedback email frequency and content and that they may opt out of correspondence at any time by informing the research team. Email templates will be developed for each of the seven time points, containing personalized dietary and PA feedback content for each participant. Feedback will be consistent with communications from the LiveLighter campaign, Australian Dietary Guidelines, and the Australian PA and Sedentary Behavior Guidelines [48-50]. The content will address each participant’s personal barriers to changing key diet and PA behaviors, reinforce motivation, and guide the adoption of health-enhancing habits. Tailored feedback on diet and PA behaviors will commence within 2 weeks of baseline and continue at 4, 6, 12, 18 weeks and 6 and 12 months thereafter. The feedback emails will be sent from Monday to Friday during business hours (9 AM to 5 PM). Components used in tailoring will include self-comparison, preference for autonomy support, intention, motivation, confidence informed by self-determination theory, and motivational interviewing (Table 2) [52,53].

